## Abstract

**Background::**

To evaluate the effect of dl-3-N-butylphthalide (NBP) on new cerebral microbleeds (CMBs) in patients with acute ischemic stroke (AIS).

**Methods::**

We will prospectively enroll patients with AIS admitted to the stroke center of Jingjiang People's Hospital. Qualified participants will be randomly assigned to either the NBP group (NBP injection) or the control group (NBP injection placebo) in a ratio of 1:1. Patients will complete the brain magnetic resonance imaging within 48 hours and 14 days after stroke onset to observe the CMBs through susceptibility weighted imaging, and evaluate whether the use of NBP will affect the new CMBs in AIS patients. SPSS 20.0 will be used for statistical analyses.

**Result::**

We will provide practical and targeted results assessing the safety of NBP for AIS patients, to provide reference for clinical use of NBP.

**Conclusion::**

The stronger evidence about the effect of NBP on new CMBs in AIS patients will be provided for clinicians.

## Introduction

1

Acute ischemic stroke (AIS) accounts for about 80% of the incidence of stroke, causing serious economic and social burdens.^[1]^ Currently, intravenous recombinant tissue plasminogen activator (rt-PA) in the early stage is the most effective drug treatment for AIS.^[2]^ Several randomized trials have confirmed that intravenous thrombolysis (IVT) within 4.5 hours of stroke onset improve the clinical outcomes of patients at 3 months.^[3–6]^ Therefore, the cerebrovascular diseases guidelines recommend rt-PA as the first-line treatment for AIS patients. For patients with large vessel occlusion stroke, the recanalization rate of IVT is relatively low. A number of studies have confirmed that endovascular therapy can significantly improve the prognosis of patients with large vessel occlusion stroke.^[7–12]^ However, some patients outside the treatment window lose the chance of thrombolysis or endovascular therapy and even in patients receiving IVT or endovascular treatment, there are still a considerable number of patients with neurological deficits that have not been significantly improved, or even cannot benefit from treatment. Therefore, there is still much room for optimization in the treatment of AIS patients, and it is necessary to find effective drugs to improve the prognosis of AIS patients.

Ischemic stroke usually presents with neurological deficits in the acute phase. Neuroprotective drugs reduce ischemic injury and improve the functional prognosis of patients by various means, and can be used as an effective adjunct to the treatment of patients with ischemic stroke. Previous studies indicated that dl-3-N-butylphthalide (NBP) not only improved neurological function, but also contributed to the long-term outcomes.^[13]^ The mechanisms of NBP for ischemic stroke treatment may involve many complex molecular mechanisms, including anti-oxidant, anti-thrombosis, anti-apoptosis, anti-inflammation, protection of mitochondria, and so on.^[14]^

NBP reduces the content of arachidonic acid and inhibit platelet aggregation and adhesion,^[15]^ which is similar to aspirin. Studies indicated that antiplatelet drugs such as aspirin increased the risk of intracranial hemorrhage^[16–18]^ and the incidence and severity of bleeding are related to the type and dosage of drugs. There were 0.9% serious intracranial hemorrhage conversion events in AIS patients treated with aspirin and clopidogrel, which was higher than 0.4% in aspirin alone group.^[18]^ Hemorrhagic transformation can be used to evaluate the safety of drugs, but no research has been conducted on the bleeding risk of NBP on AIS.

Most of the present research on the safety of AIS treatment drugs is based on symptomatic intracranial hemorrhage (sICH), however, the incidence of sICH is relatively low, which affects the sensitivity of the study. Patients with AIS will develop tiny bleeding lesions that cannot be detected by conventional computed tomography (CT) in the acute phase. These new tiny bleeding lesions detected by susceptibility weighted imaging (SWI) are called new cerebral microbleeds (CMBs).^[19]^ Studies have found that CMBs is a risk factor for sICH, and patients with CMBs are more prone to develop sICH. In patients with ischemic stroke, the incidence of new CMBs is 4.4% to 24.5%,^[20–22]^ which is significantly higher than that of sICH. Therefore, the use of new CMBs to evaluate drug safety for AIS has higher sensitivity. Studies confirmed that aspirin increased the risk of new CMBs.^[23,24]^ NBP reduces the content of arachidonic acid and inhibit platelet aggregation and adhesion, which is similar to aspirin. Therefore, NBP may increase new CMBs in AIS patients. However, NBP can reduce the inflammatory response of AIS and promote blood vessel regeneration after infarction and reduce infarct volume, and studies have shown that the inflammation and infarct volume are risk factors for CMBs,^[25,26]^ suggesting that NBP may reduce new CMBs in AIS. Therefore, it is impossible to speculate the effect of NBP on the new CMBs of AIS. Given that CMBs is a risk factor for intracranial hemorrhage, it is necessary to evaluate whether the use of NBP will increase the new CMBs in patients with AIS.

In this study, we will prospectively include patients with AIS, randomly divide them into an observation group (NBP) and a control group (NBP placebo) and evaluate the effect of NBP on new CMBs.

## Methods

2

### Study design

2.1

This is a study protocol for a prospective randomized controlled trail that follows SPIRIT 2013 statement: defining standard protocol items for clinical trials and CONSORT 2010 Statement: updated guidelines for reporting parallel group randomized trials.^[27,28]^

This study will be conducted at the Jingjiang People's Hospital and use new CMBs as indicators to evaluate the safety of NBP in patients with AIS. We will enroll patients with AIS and randomly divided them into the control group and the observation group. The control group will be treated according to the guidelines for AIS and the observation group will be given additional NBP. Patients will complete the brain magnetic resonance imaging (MRI) within 48 hours and 14 days after stroke onset to observe the new CMBs through SWI, and evaluate whether the use of NBP will affect the new CMBs in AIS patients (Figs. 1 and 2). Each participant will be required to sign an informed consent form before enrollment. In addition, they all have the right to withdraw from the study at any time.

**Figure 1 F1:**
[figure not shown]
The flowchart of the study protocol.

**Figure 2 F2:**
[figure not shown]
Standard protocol items.

### Ethics

2.2

The study has been approved by the Ethics Committee of Jingjiang People's Hospital (No. 2020-01-006), and it has been registered under the identifier No. ChiCTR2000033486 on the Chinese Clinical Trial Registry on 2020-06-02. Any modifications to the research protocol will be notified to this Human Research Ethics Committee. Informed consent will be obtained from each participant before enrollment. The study bases on the principles of the Declaration of Helsinki and Good Clinical Practice guidelines.

### Recruitment

2.3

We will prospectively enroll patients with AIS admitted to the stroke center of Jingjiang People's Hospital. The diagnosis of AIS is according to the World Health Organization criteria^[29]^ and confirmed by brain CT or MRI.

### Sample size

2.4

We used EpiCalc 2000 for sample size estimation, set significance = 0.05, power = 80%, ratio of cases to controls = 1, risk ratio to detect = 2, proportion (%) controls exposed = 15% (4.4%–24.5%). The sample size was 207 in each of the observation group and the control group.

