### Data analysis

3.7

Statistical analyses will be conducted with SPSS version 20.0 software (SPSS, Chicago, IL). Statistical differences between the 2 groups will be tested using Student *t* test for normally distributed variables or Fisher exact test for dichotomous variables. Two-tailed *P* values < .05 will be considered statistically significant.

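### The stated inputs (risk ratio 2, 15% in controls) require 121 per group, not 207; 207 matches an odds ratio of 2, so the target effect and power need restating

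*Protocol article*

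**What the plan says.** The inputs in section 2.4 (Sample size) are: "set significance = 0.05, power = 80%, ratio of cases to controls = 1". The target effect and the result follow: "risk ratio to detect = 2, proportion (%) controls exposed = 15% (4.4%–24.5%). The sample size was 207 in each" of the observation and control groups. The section does not give the event rate assumed in the NBP group, and it does not name the formula or test behind the calculation.

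Section 3.7 (Data analysis) supplies the two remaining elements. The sidedness is fixed by "Two-tailed *P* values < .05 will be considered statistically significant". The test for a binary outcome, such as the presence of any new microbleed, is the "Fisher exact test for dichotomous variables".

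**The concern.** Effect, control rate, significance level, power and group size are all printed, so the result can be recomputed. For a doubling of a 15% risk at 80% power, 207 per group looks far too large. The vocabulary is also out of place in a randomised trial: "ratio of cases to controls = 1" and a proportion of controls exposed are the inputs of a case-control calculation, in which the effect measure is an odds ratio. At a control rate of 15%, an odds ratio of 2 and a risk ratio of 2 are clearly different effects.

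At stake is what a reader may conclude about the effect the trial can detect. The Discussion intends to read an absence of effect on new microbleeds as confirmation of safety. A null result can only be judged against the effect that the trial was sized to find and the power it had for that effect. Section 2.4 should supply both, and as written it does not supply a consistent pair.

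**Working it through.** **Inputs.** From section 2.4: significance level 0.05, power 80%, ratio 1:1, control rate p0 = 0.15, effect 2, result 207 per group. From section 3.7: two-sided testing and Fisher's exact test for binary outcomes.

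**Formula.** The standard size per group for comparing two proportions, without continuity correction, is

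n = [1.960 × √(2m(1 − m)) + 0.8416 × √(p0(1 − p0) + p1(1 − p1))]² / (p1 − p0)², where m = (p0 + p1)/2.

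With continuity correction, n_c = (n/4) × [1 + √(1 + 4/(n(p1 − p0)))]².

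**Step 1: the plan's figure from its stated inputs.** A risk ratio of 2 gives p1 = 2 × 0.15 = 0.30 and m = 0.225.

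- n = (1.960 × 0.5906 + 0.8416 × 0.5809)² / 0.15² = (1.1575 + 0.4889)² / 0.0225 = 120.5, so 121 per group.
- With continuity correction, n_c = 133.5, so 134 per group.

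The stated 207 is not reproduced. Other common variants for 15% versus 30% at 80% power do not reach it either: unpooled variance 118, Kelsey 122, arcsine 119, one-sided 95 (108 with correction). Reading the ratio in the other direction (risk ratio 0.5) gives 278 or 304 two-sided and 219 or 245 one-sided.

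**Step 2: the effect read as an odds ratio.** An odds ratio of 2 gives p1 = 2 × 0.15 / (1 + 0.15) = 0.30/1.15 = 0.2609. The implied risk ratio is 0.2609/0.15 = 1.74, and m = 0.2054.

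- n = (1.960 × 0.5714 + 0.8416 × 0.5660)² / 0.1109² = (1.1199 + 0.4763)² / 0.01229 = 207.3.
- With continuity correction, n_c = 225.

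The uncorrected result, rounded to the nearest whole number, is the stated 207.

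**Step 3: other routes to a figure near 207.** For a true risk ratio of 2, one would need a control rate of about 9.7%, or about 40% loss added to the uncorrected 121 (which gives 202). A third route is 95% power with continuity correction (212). Each contradicts the printed inputs or uses one that is not printed.

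**Step 4: power at 207 per group.** Exact power was found by enumerating all pairs of event counts and rejecting when the two-sided P value is below 0.05.

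| True rates | Fisher's exact test | Uncorrected chi-square test |
|---|---|---|
| 15% vs 30% (risk ratio 2) | 94.8% | 95.9% |
| 15% vs 26.1% (odds ratio 2) | 76.9% | 80.2% |

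The normal approximation gives 95.8% and 79.9% for the two rows. At an odds ratio of 2, Fisher's test reaches 80% at about 223 per group.

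**The case against.** The best defence is that nothing harmful follows. For the only effect that section 2.4 names, "risk ratio to detect = 2", 207 per group is more than enough: Fisher's test has 94.8% power. Its conservatism protects the type I error rate, and no analysis result would change. This stands. A reader who sees that the calculation fails might infer that the trial is underpowered or must enrol more patients. The documents do not support that. Power falls below 80% only at 15% versus 26.1%, rates that the protocol does not print. Even there the gap is 3.1 percentage points, or about 16 patients per group (223 − 207).

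It is also fair to object that the protocol nowhere mentions an odds ratio. The agreement in Step 2 and the case-control wording make that origin likely, but it remains an inference. The document cannot show whether a risk ratio of 2 was intended and put through the wrong module, or an odds ratio was intended and mislabelled. The remedy must therefore leave both readings open.

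Neither objection removes the basic fault: the printed inputs do not give the printed size. This is not a detail that a journal article leaves to a fuller document, because every quantity needed is stated.

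**Conclusion.** The sample-size statement is wrong as written. Its own inputs require 121 per group (134 with continuity correction) against a stated 207, which is 1.7 times the uncorrected figure (207/121). The most likely explanation is an odds ratio of 2 labelled as a risk ratio, sized for an uncorrected chi-square test. The mismatch with the planned Fisher test is secondary: it takes power from 80% to about 77% under that explanation, and has no practical consequence under the stated risk ratio.

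The conclusion that 207 does not follow from the inputs rests on printed figures alone. The odds-ratio explanation rests on a numerical match and on wording. The power figures assume a true control rate of 15% and 207 evaluable patients per group. The point is that the target effect and its power are misstated, not that the trial is too small.

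**What to change.** Restate section 2.4 so that it names the effect measure, gives the assumed rate in both groups, and states the power of the test that will be used. Two consistent versions are available, and the investigators should choose the one that reflects their intention:

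- Keep the risk ratio of 2, write it as 15% versus 30%, and state that 207 per group gives about 95% power with Fisher's exact test.
- State an odds ratio of 2, write it as 15% versus 26.1% (risk ratio 1.74), and state about 77% power with Fisher's exact test. If 80% is to be kept, name the uncorrected chi-square test as the test for the primary outcome in section 3.7.

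The change is to text only and needs no extra enrolment. The cost is that a published figure has to be corrected; under the second version with Fisher's test, the stated power becomes slightly less favourable.

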### Randomization

2.5

Qualified participants will be randomly assigned to either the NBP group or the control group in a ratio of 1:1. Random numbers will be generated by a random number generator in the SPSS version 20.0 software (SPSS, Chicago, IL), which will be operated by a third party who is uninvolved with the treatment and data collection. The drawn letters (A or B) will be placed into opaque envelopes labeled with sequential numbers. The envelopes will be sealed and remain in numerical order in a safe place till the completion of this study. The same researcher (not involved in the study) will prepare the envelopes.

### Blinding

2.6

In this single-blind study, NBP injection and NBP injection placebo will be produced by CSPC NBP Pharmaceutical Co., Ltd, vensuring that the patients included in the study completely do not know which goods they will receive.

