### Treatment

3.1

Patients will be grouped immediately after being included in the study. The observation group and the control group will be given NBP injection and NBP injection placebo, respectively, for 14 consecutive days, twice per day. The first injection NBP/NBP placebo should be within 6 hours of stroke onset. In the process of intravenous infusion, a non-PVC infusion set (uniformly equipped by CSPC NBP Pharmaceutical Co., Ltd) must be used. The infusion of NBP time is not less than 50 minutes, and the interval between 2 infusions is not less than 6 hours. If the first infusion start time is after 16:00, then the first day will be given NBP/NBP placebo only once, otherwise 2 times of drugs will be usually given.

We will follow the Chinese guidelines for management of AIS.^[30]^ All patients will receive standards of care, including IVT, endovascular treatment, antiplatelet or anticoagulant therapy based on the patient's condition, nutritional support, and dealing with complications.

Avoid using elixirin, edaravone, or Chinese patent medicine injection containing ginkgo biloba and its extracts during the study. Other medical treatment recommended by the “Chinese Guidelines for the Diagnosis and Treatment of Acute Ischemic Stroke” is permitted.

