### Outcome assessment

3.4

The outcomes will be assessed by independent assessors, who had been trained before participating in this study and blinded to the randomization. All outcome data for participants whether completed or withdrawn during the study will be collected and recorded in the case report form.

Primary outcome: to evaluate the effect of NBP on new CMBs in patients with AIS.

Secondary outcome: to evaluate the effect of NBP on sICH and the National Institute of Health stroke scale score at 14 days of onset.

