### Adverse events

3.5

From the time the patient is enrolled to the last follow-up, any adverse medical events regardless of whether they are causally related to the test drug, will be determined to be adverse events. The researchers will record and report all adverse events. The record includes the occurrence time, severity, duration, measures and outcomes of the adverse events, and separate explanation its potential related drugs.

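### The trial is declared single-blind: no passage blinds care, infusion or adverse-event staff, although a matched placebo exists and antithrombotic co-treatment can change the primary outcome

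*Protocol article*

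**What the plan says.** All references are to the Protocol article.

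- **Section 2.6, Blinding:** "In this single-blind study, NBP injection and NBP injection placebo will be produced by CSPC NBP Pharmaceutical Co., Ltd". The stated aim is that "the patients included in the study completely do not know which goods they will receive". No other group is named there.
- **Section 3.4, Outcome assessment:** outcomes are judged by independent assessors "who had been trained before participating in this study and blinded to the randomization".
- **Section 2.5, Randomization:** a third party with no part in treatment or data collection runs the random numbers. "The drawn letters (A or B) will be placed into opaque envelopes labeled with sequential numbers". The envelopes are to stay sealed until the study is finished.
- **Section 2.8, Test drugs:** the placebo has the same volume (100 mL), sodium chloride content (0.9 g) and manufacturer as the active product, with 0 mg NBP.
- **Section 3.1, Treatment:** both arms follow the national stroke guideline, with "antiplatelet or anticoagulant therapy based on the patient's condition".
- **Section 3.5, Adverse events:** "The researchers will record and report all adverse events", with a "separate explanation its potential related drugs". Neither the role nor the blinding of these researchers is given.
- **Section 1, Introduction:** aspirin is said to raise the risk of new CMBs, and NBP's antiplatelet action is likened to that of aspirin.

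**The concern.** The primary outcome is new CMBs at 14 days, and the protocol itself treats antiplatelet drugs as a cause of them. Antithrombotic treatment is chosen during the same 14 days, after randomisation. If those who choose it know the arm, exposure to a known cause of the outcome can differ between arms for reasons other than NBP.

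Blinded SWI reading protects the counting of lesions. It does not protect against lesions that were caused or prevented by unequal co-treatment.

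The stakes are higher because of how a neutral result will be used: the Discussion says that a finding of no effect will confirm the safety of NBP. A bias that shrinks a true excess would support that statement wrongly. The drug-causality explanation required for each adverse event is likewise open to influence if the recorder knows the arm.

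**Working it through.** **1. Who is blinded.**

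| Group | What the article says |
|---|---|
| Patients | Blinded (2.6) |
| Outcome assessors | Independent and blinded (3.4) |
| Treating clinicians | Not stated; the trial is called single-blind (2.6) |
| Infusion staff | Not stated |
| Adverse-event recorders | Called researchers; blinding not stated (3.5) |

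Read literally, section 2.5 keeps the letters sealed to the end, which would fit wider concealment than section 2.6 declares. If staff see only a letter, the single-blind label understates the design. If staff do know the arm, the purpose of keeping envelopes sealed is unclear. The sections need reconciling on either reading.

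**2. The plan's own figure.** Inputs from section 2.4: control rate p0 = 0.15, two-sided 0.05, power 80%, 1:1, effect 2, stated n = 207 per group.

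Reading 2 as an odds ratio: p1 = (2 × 0.15/0.85) / (1 + 2 × 0.15/0.85) = 0.3529/1.3529 = 0.261.

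n = [1.960 √(2 p̄(1 − p̄)) + 0.842 √(p0(1 − p0) + p1(1 − p1))]² / (p1 − p0)², with p̄ = 0.2054:

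n = (1.120 + 0.476)² / 0.1109² = 207.3, or 208 when rounded up. This reproduces 207.

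Reading 2 as a risk ratio, as labelled (30% versus 15%), the same formula gives 121, or 134 with continuity correction. The stated size therefore matches the odds-ratio reading, which is used below with the risk-ratio reading alongside. Blinding more staff does not change n.

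**3. Illustration of co-treatment bias.** The following inputs are assumptions; the document gives none of them. A share s of NBP patients receives less intensive antithrombotic therapy because the arm is known, and their new-CMB risk falls by a fraction r. Then

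observed NBP rate = p1 × (1 − s·r).

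With s from 10% to 30% and r from 30% to 50%, the factor runs from 1 − 0.10 × 0.30 = 0.97 to 1 − 0.30 × 0.50 = 0.85.

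Power is for the two-sided Fisher test named in section 3.7, applied to the proportion with any new CMB. It is the sum, over all outcome pairs at 207 per arm, of the binomial probabilities of pairs with p < 0.05.

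| True NBP rate | s, r | Observed NBP rate | Observed risk ratio | Fisher power |
|---|---|---|---|---|
| 26.1% (odds ratio 2) | none | 26.1% | 1.74 | 77% |
| 26.1% | 10%, 30% | 25.3% | 1.69 | 71% |
| 26.1% | 20%, 50% | 23.5% | 1.57 | 55% |
| 26.1% | 30%, 50% | 22.2% | 1.48 | 42% |
| 30% (risk ratio 2) | none | 30.0% | 2.00 | 95% |
| 30% | 10%, 30% | 29.1% | 1.94 | 92% |
| 30% | 30%, 50% | 25.5% | 1.70 | 72% |

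By the normal approximation the corresponding figures are 79.9% falling to 47–75% for the odds-ratio reading, and 95.8% falling to 76–94% for the risk-ratio reading. With no true effect, the same factors give an apparent risk ratio of 0.85 to 0.97.

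**The case against.** The strongest reply is that a patient-blind, assessor-blind trial is a disclosed and respectable design. Two SWI scans are planned for every patient, two readers judge them and a third settles disagreements. The arms share one guideline, and antithrombotics are to follow the patient's condition, not the arm. The protocol also argues that NBP might reduce CMBs, so it gives clinicians no one-sided reason to hold treatment back. The power figures rest on invented inputs, and at the mild end the loss is only about six points (77% to 71%). Kit labelling and code-break rules are details that an article may leave to the full protocol.

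Much of this stands, and it rules out several stronger readings that a reader might infer:

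- **Treating clinicians know the arm.** No passage says so. It is an inference from the word single-blind, and the sealed envelopes may point the other way.
- **Treating clinicians record adverse events.** Section 3.5 says researchers, without giving their role.
- **One disclosed patient reveals every allocation.** That needs the shared letter to be on the drug supplies. Section 2.5 puts it only in envelopes.
- **sICH detection depends on scans ordered by unblinded staff.** The document describes no such scans, and outcome assessors are blinded.
- **The bias probably runs towards no harm.** The direction in the table follows from the assumed step-down; the text does not establish it.

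What the reply does not answer is the co-treatment path. Condition-based prescribing still leaves judgement, and blinded reading acts after that judgement has had its effect. Nor is the blinding level a detail lost in condensing: the article states it and limits it to patients and assessors.

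**Conclusion.** The point holds in limited form. The article declares a single-blind trial and extends blinding only to patients and outcome assessors, although a volume-matched placebo and an uninvolved third party are already in place. Because antithrombotic choice is individual and the protocol links aspirin to new CMBs, staff who know the arm could bias the primary comparison in a way that blinded reading cannot correct. Sections 2.5, 2.6 and 3.4 also do not give one clear account of who is blinded.

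The size is unknown. The fall in Fisher power from 77% to about 42–71% depends wholly on the assumed 10–30% step-down, the assumed 30–50% risk reduction and the odds-ratio reading of section 2.4. Under the risk-ratio reading, power starts at 95% and stays at about 72–92%. These figures show that the mechanism could matter; they do not show that it will operate. The change should be made, because it is cheap and protects the main comparison.

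**What to change.** - In section 2.6, list every blinded group and add treating clinicians, infusion staff and adverse-event recorders to patients and outcome assessors. Replace the single-blind label accordingly.
- In section 2.5, have the uninvolved third party label each patient's supply with a unique kit number and hold the code for emergency unblinding. State what the sealed envelopes are for, so that sections 2.5, 2.6 and 3.4 agree.
- Record antithrombotic exposure during the 14 days and compare it between arms, as a check on co-treatment.
- If some staff cannot be blinded, name them, and keep them out of adverse-event causality judgements.

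**Cost:** relabelling of supplies, an emergency code-break procedure, and revised wording in sections 2.5 and 2.6. Sample size, study drug and clinical rules are unchanged.
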